### Methods against bias

To compare inpatient and day clinic samples, a parallelization according to known predictors of outcome [14] will be conducted: (1) Gender [m;f], (2) age [<40; >=40: mean age in previous studies], (3) number of additional axis-I diagnoses [<2; >=2], (4) number of previous episodes of major depression [0; <=2; >2] and (5) duration of the recent episode of MDE [<6 months; 6–24 mo >24 mo]. Criteria (1) to (3) will be matched 1:1; criteria (4) & (5) are used as lenient criteria, to be matched 1:1 if possible, otherwise the extremes may not be matched together. We expect a loss of about 20% due to “mismatches”, missing data and patients dropping out of the study.

Antidepressant medication, the initial score of the QIDS-C and the number of psychotherapy sessions following discharge will be controlled for in the final analysis. At the end of the study, patients screened and not taking part and patients taking part in the study will be compared, as well as patients dropping out of the study with those completing the study.

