There are few naturalistic studies describing effects of psychosomatic inpatient and day hospital treatment, mostly lacking follow-up assessments and a detailed description of patients characteristics (personality, co-morbidity) [4-6,10-12]. The majority of studies report on heterogeneous samples including depressed patients besides other diagnoses. There is no study trying to identify subgroups of patients with a main diagnosis of major depression with different symptom courses and no study comparing inpatient and day hospital treatment. The same is true for psychiatry, with a limited number of studies on this topic conducted in the German health care system (see for example: [13-15]).

The following predictors were repeatedly found to be associated with the course and overall outcome in depression: (1) number of episodes of major depression (MDE), (2) duration of the current MDE, (3) co-morbidity (mental, somatic) and (4) incomplete remission of the last episode of MDE or “double depression” [3]. A higher probability for a relapse is associated with younger age, female gender, a lack of social support and being single. An additional somatic illness and a late onset of treatment are able to nearly completely explain prognosis in a higher age group [16]. Traumatic childhood experiences were also identified as a risk factor for depression and important to consider in terms of the long term course and risk for relapse [17]. Most of these factors have been found in studies on outpatient treatment for depression. It remains unclear, if the same predictors will be identified analysing samples of patients treated within an inpatient or day hospital setting.

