Another group of studies focusses on the influence of personality characteristics on the course and prognosis of depression. One of the most relevant concepts in this field is the one of Sydney Blatt, who postulated a two-dimensional model, which differentiates between depressed patients who primarily deal with problems in interpersonal relatedness (“anaclitic”: fears of abandonment; dependency) and those preoccupied with self-definitional issues (“introjective”: hash self-criticism; perfectionism) [18]. There is an ongoing debate on the relevance of this theoretic model^a^. In support of it, perfectionism as a trait was repeatedly found to be associated with a more problematic course in depression. Overall, it can be assumed that personality traits and other patient variables (social support, interpersonal problems, etc.) are not only overall predictors of outcome, but also interact with the form of treatment or setting provided.

Studies comparing inpatient and day hospital treatment found comparable outcomes for patients with mental disorders, for whom both settings are suitable [8]. We could replicate this finding for a psychosomatic clinic in Germany [11], but found differences in effects when analysing outcome for single diagnostic categories like eating disorders [19,20]. Comparing means of large samples might cover differences between subgroups, which can be better treated in one or the other setting. In a pilot study, we tried to identify predictors of differential outcome of inpatient and day hospital treatment and found a higher motivation for psychotherapy and higher burdens at home to be associated with a good outcome after day hospital treatment, whereas strong wishes to give up responsibility for oneself were associated with an unfavourable course of inpatient treatment [5,21]. Strong wishes to give up responsibility might be associated with “anaclitic” features according to S. Blatt et al. [18], but this has to be shown empirically.

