### Measurement time points

Time points of measurement will be the time point at admission (T0), at discharge (T1), a three months follow-up (T2) and a 12 months follow-up (T3). Data will include a detailed assessment on different levels: symptomatology (characteristics of depression and co-morbid conditions), general disturbance and quality of life, aspects of personality, interpersonal problems and a further aspects that has been identified to influence the course of depression: traumatic childhood experiences. Variables will be grouped into classes of possible predictors. A combination of self-report and assessments by independent, trained research assistants will be used (see Table 2).

**Table 2 T2:** Instruments used the INDDEP study

**Time point of measurement**	**Outcome/Variables**	**Patient**	**Research assistant**
		**(self-report)**	**(expert rating)**
**T0 **(admission)	Depressive symptomatology:	QIDS-SR	QIDS-C, SKID-I
	Co-morbidity		SCID I + II
	Personality, interpersonal problems, mode of coping:	IIP-32, DEQ, DAS	
	Overall disturbance and functioning:	SCL-90-R	SOFAS
	Social support:	F-SozU K-14	
	Quality of Life:	SF-12	
	Traumatisation:	CTQ	
**T1 **(discharge)		QIDS-SR	QIDS-C
		SCL-90-R	SOFAS
		IIP-32	
**T2 **(3-months Follow-up) and **T3 **(12-months Follow-up)		QIDS-SR	QIDS-C, LIFE-Interview
		SCL-90-R	SOFAS
		SF-12	
		IIP-32	

QIDS-SR = Quick Inventory of Depressive Symptoms, self-report form [23], QIDS-C = expert rating; SCID-I and SCID-II=Structured Clinical Interview for DSM IV axis I and II [24,25]; SCL-90-R = Symptom-Check-List 90-R [26]; DAS = Dysfunctional Attitudes Scale [27,28]; DEQ = Depressive Experiences Questionnaire [29,30]; SOFAS = Social and Occupational Functioning Assessment Scale [31]; IIP-32 = Inventory of Interpersonal Problems, 32-item version [32,33]; F-SozU K-14 = Fragebogen zur sozialen Unterstützung, 14-item version [34]; SF-12 = Fragebogen zum Gesundheitszustand (quality of life) [35]; CTQ = Childhood Trauma Questionnaire [36,37]; LIFE-Interview = Longitudinal Interval Follow-up Evaluation [38].

Note: Additionally assessed at all time points of measurement: pharmacological treatment, somatic diagnoses; at T0: previous treatment for depression; at T1: documentation of treatment received (dose, components); T2 and T3: further outpatient treatment, days of sick leave, number of contacts to health care system.

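### The stated bias control for the setting comparison leaves out double depression and somatic co-morbidity, and nothing stated repairs permitted mismatches on episodes and episode duration

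*Protocol article*

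**What the plan says.** The Background (Protocol article) names four predictors repeatedly found to go with the course and overall outcome of depression. The list opens with "1) number of episodes of major depression (MDE), (2) duration of the current MDE, (3) co-morbidity (mental, somatic" and ends with "incomplete remission of the last episode of MDE" or double depression. Separately, it links younger age, female gender, poor social support and being single to relapse, and childhood trauma to depression risk, long-term course and relapse.

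The section Methods against bias says the two samples will be made parallel on known outcome predictors and then fixes the set:

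- Gender, age (below 40, or 40 and above) and number of additional axis-I diagnoses (below 2, or 2 and above) are strict: "Criteria (1) to (3) will be matched 1:1".
- Previous episodes (three categories) and duration of the current episode (three categories) "are used as lenient criteria, to be matched 1:1 if possible, otherwise the extremes may not be matched together".
- "Antidepressant medication, the initial score of the QIDS-C and the number of psychotherapy sessions following discharge will be controlled for in the final analysis".

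Table 2 and its note (Measurement time points) show that SCID-I and SCID-II, the F-SozU ("Social support"), the CTQ and somatic diagnoses are all obtained at admission. The Discussion adds socio-demographic data.

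**The concern.** The plan sets its own standard, balance on known predictors of outcome, and the set it fixes falls short of the list in its own Background. Patients reach a setting by routine clinical decision and preference, not by chance. A baseline variable that differs between settings and also predicts QIDS-C change will be read as part of the setting effect unless it is balanced or adjusted for. The target is a small effect (d = 0.2), so a modest residual difference can matter. Most of the omitted information is collected at admission anyway.

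**Working it through.** **Step 1. Set the Background's four predictors against the stated bias control.**

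| Predictor in Background | Matched? | Named control? | Available at T0? |
|---|---|---|---|
| Number of episodes | Leniently; neighbouring categories may be paired | No | Yes, needed to form the matching categories |
| Duration of current episode | Leniently; neighbouring categories may be paired | No | Yes, same reason |
| Mental co-morbidity | Strictly, as a two-level axis-I count | No | SCID-I and II |
| Somatic co-morbidity | No | No | Somatic diagnoses, all time points |
| Incomplete remission/double depression | No | No | Derivable from SCID-I |

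Of the three named controls, baseline QIDS-C covers initial severity and none covers illness history or somatic illness. Post-discharge sessions arise after treatment and cannot stand in for a baseline predictor.

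**Step 2. Do other sections fill the gap?** Sample size calculation mentions covariates, but for precision. Statistical analysis describes predictor selection in the hierarchical model and in the categorical regression. Neither says that these covariates form the confounder set for the setting contrast.

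**Step 3. Possible size for one omitted predictor.** The plan has no figure for residual imbalance, so there is nothing of its own to reproduce. Inputs:

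- target d = 0.2 and 300 per group, with 10% attrition and 20% mismatch loss (Sample size calculation);
- analysed number: 300 × 0.9 × 0.8 = 216 per group;
- assumed, not in the document: imbalance 0.1 to 0.5 SD; standardised slope on outcome 0.1 to 0.3.

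Bias in outcome SD = slope × imbalance.

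- Lowest: 0.1 × 0.1 = 0.01, which is 0.01/0.2 = 5% of the target.
- Middle: 0.2 × 0.3 = 0.06, or 30%.
- Highest: 0.3 × 0.5 = 0.15, or 75%.

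With standard error √(2/216) = 0.096 SD, the chance of a false positive at a nominal two-sided 5% is P(|Z + bias/0.096| > 1.96). This is 5.1%, 9.6% and 34% in the three cases.

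**Step 4. Mismatch on a lenient criterion.** Assume three equally filled categories scored 0, 1, 2, with SD √(2/3) = 0.816. If a share q of pairs is off by one category, all in the same direction, the imbalance is q/0.816.

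- q = 0.1 gives 0.12 SD.
- q = 0.5 gives 0.61 SD.

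Multiplied by slopes of 0.1 to 0.3, the bias is 0.01 to 0.18 SD. If mismatches fall equally in both directions, it is about zero.

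**Step 5. Cost of adjusting.** The SE ratio after adding k covariates is √[(1 − R²outcome)/(1 − R²setting) × (N − 2)/(N − 2 − k)], with N = 2 × 216 = 432 and, for illustration, k = 6.

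- They explain no outcome variance and are balanced: √(430/424) = 1.007.
- They explain 10% of outcome and are balanced: √(0.9 × 430/424) = 0.955.
- They explain none of the outcome and 10% of setting: √[(1/0.9) × 430/424] = 1.062, the worst case tried.

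**The case against.** The best defence is that the section says three variables will be controlled for, not that only these will be. Covariates are foreseen elsewhere, and a fuller protocol or analysis plan may name more. That would settle the matter if the article were merely silent. It is not: under a heading about bias it fixes five matching variables with cut-points and three controls, and the covariates mentioned elsewhere serve precision or predictor discovery.

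A second defence is that the Background itself says most of these predictors come from outpatient studies and may not carry over to hospital samples. The caution is fair, but it applies equally to the predictors that are matched, so it does not explain why two of the four are left out.

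Several stronger readings are tempting and are not supported:

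- **The leniently matched predictors are the strongest ones.** The Background lists episodes and duration first but does not rank by strength.
- **Episodes and duration may mismatch freely.** Pairing of extremes is barred, exact matching is tried first, and a mismatch biases the contrast only if it leans one way.
- **Social support, being single and childhood trauma are equally serious omissions.** The document ties them to relapse, depression risk or long-term course, while the stated dimensional outcome is change to three months.
- **Unmeasured motivation and home burden drive setting choice.** The pilot "found a higher motivation for psychotherapy and higher burdens at home to be associated with a good outcome after day hospital treatment"; that is differential outcome, not selection into a setting. Absence from Table 2 does not prove they are not collected, since socio-demographic data are absent there too.
- **Centre is ignored.** It is handled by nesting and by a minimum of 35 patients per setting and centre.

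The document also openly calls the comparison quasi-experimental and does not claim to remove all bias.

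**Conclusion.** The point holds in a limited form. Of the four predictors the Background calls repeatedly found, incomplete remission/double depression and somatic co-morbidity are neither matched nor named for adjustment in the setting comparison. Permitted one-category mismatches on episodes and duration have no stated correction.

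A reader might infer from the arithmetic that the setting effect will be biased by a known amount, or that several omissions add up to the target effect. The document supports neither. The range of 0.01 to 0.15 SD per predictor rests wholly on assumed imbalances and slopes, taken to apply after matching and baseline adjustment, and summing would further assume a common direction and no overlap. What can be said is that the size is unknown, that plausible values are not negligible against d = 0.2, and that the remedy is cheap, though not strictly free.

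**What to change.** Keep the matching. In the hierarchical model for the inpatient versus day hospital contrast, pre-specify as baseline covariates:

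1. number of episodes and episode duration as actual values, which also picks up differences within the matching categories;
2. double depression, derived from SCID-I;
3. somatic co-morbidity, from the somatic diagnoses at admission.

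As secondary additions, mainly for the 12-month course, include social support (F-SozU), childhood trauma (CTQ) and partner status, the last if the socio-demographic data record it. State that these covariates are there to control confounding and are kept whatever the predictor-selection step retains. Report standardised differences between settings after matching for all of them.

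The cost is analysis wording and a few degrees of freedom. All seven covariates together, if uninformative and balanced, would widen the standard error by √(430/423) = 1.008. If they explained 10% of setting and nothing of outcome, the loss would be about 6%. If they explain outcome and are balanced, precision improves slightly. No new instrument is needed.

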## Methods

For to analyse a sample which represents the clinical reality of psychosomatic inpatient and day hospital treatment for depression in Germany (external validity), we did not choose a randomized design as we expected only a minority of patients to agree to a randomization procedure and expected considerable resistance in non-university centres. Therefore, the study is naturalistic in nature and composes two steps: I) an analysis of predictors in the whole sample and II) a comparison of inpatient and day clinic treatment in a quasi-experimental design. For a comparison of inpatient and day clinic treatment, samples will be parallelized according to known predictors of outcome (see: methods against bias).

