### Participants

During a 2.5-year recruitment period, all patients admitted to the participating clinics will be screened for depressive symptoms and inclusion and exclusion criteria checked. Recruitment will be continued until a sample of 300 patients is reached in each setting (inpatient, day hospital). There has to be a minimum of 35 patients per setting in each centre to control for centre effects. Research assistants will be involved, if a depression can be identified as the main reason for admission or the most dominant problem (main diagnosis). The research assistant will inform the patient about the study and check inclusion and exclusion criteria. Inclusion and exclusion criteria are listed in Table 1. Patients will get comprehensive information about the study and are included after written consent. There is permission from the local ethics committees.

**Table 1 T1:** Inclusion and exclusion criteria of the INDDEP-study

Inclusion criteria	• MDE (major depressive episode, unipolar, according to DSM IV) as main diagnosis
	• age 18-65
	• QIDS-C score > 10
	• informed consent
	• sufficient knowledge of German language
Exclusion criteria	• psychotic disorder (current or life time)
	• bipolar disorder
	• substance dependency (current or last three years)
	• current suicidal ideation
	• antisocial personality disorder
	• cognitive impairment, dementia
	• admission for diagnostic reasons (not for treatment)
	• second admission during recruitment period

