### Statistical analysis

The statistical analysis will follow the example of Fournier et al. [22]. The continuous outcome (QIDS-C) will be analyzed with hierarchical linear models (HLM; nested random effects). The difference (T0-T2) will be controlled for baseline (T0) severity. Moderator and mediator analyses will be conducted according to Kraemer et al. [41]. The analysis of categorical outcome (remission classes) will be conducted with categorical regression with methods of optimal scaling (SPSS-CatReg) [42]. The identification of predictors with SPSS-CatReg is based on boot-strapping procedures or on the “Least Absolute Shrinkage and Selection Operators” [42]. For the HLM we will adapt the example of Fournier et al. [22] restricting the degrees of freedom of the selection of predictors in a hierarchical process.

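### The non-randomised setting comparison names one QIDS-C rating to control baseline severity, although QIDS-SR is also taken at admission and would reduce any residual severity confounding

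*Protocol article*

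**What the plan says.** The Methods section explains that "we did not choose a randomized design as we expected only a minority of patients to agree to a randomization procedure", so the two settings are compared in matched samples. Under Methods against bias, the matching variables are gender, age, number of additional axis-I diagnoses, number of previous episodes and duration of the current episode, and "Criteria (1) to (3) will be matched 1:1; criteria (4) & (5) are used as lenient criteria". Symptom severity is not among them. Severity enters by regression instead: "Antidepressant medication, the initial score of the QIDS-C and the number of psychotherapy sessions following discharge will be controlled for".

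Under Statistical analysis, the hierarchical linear model is described with the words "The difference (T0-T2) will be controlled for baseline (T0) severity", and no instrument is named there. Table 2 (Measurement time points) lists both forms of the same scale at admission; its legend reads "QIDS-SR = Quick Inventory of Depressive Symptoms, self-report form [23], QIDS-C = expert rating". SCL-90-R and SOFAS are also taken at T0. On the predictor analysis, the same section says that "Variables will be grouped into classes of possible predictors". The QIDS-C at admission also decides entry ("QIDS-C score > 10", Table 1), and change on it to the three-month follow-up is the main outcome.

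**The concern.** In a randomised trial, error in a baseline covariate costs some precision. In a non-randomised comparison it can also cost validity: adjusting for an error-prone score removes only the share of a true severity difference that the score captures. The rest is attributed to the setting, and the setting with the more severe patients looks worse than it is.

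The second aim has a milder version of the problem. The Background says the study wants to go beyond depressive symptomatology to personality, coping and interpersonal problems. If severity is represented by one rating only, a questionnaire that correlates with true severity can pick up what the rating missed. A claim that it predicts beyond symptomatology would then be hard to defend.

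A second measure of the same construct is already collected at T0, and the article does not name it for severity control.

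**Working it through.** **No plan figure to reproduce.** The article states no reliability, no expected severity gap and no residual bias. The only yardstick is the standardised difference d = 0.2 under Sample size calculation.

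**Inputs, all assumed except where noted**
- λ, reliability of one rating: 0.6 to 0.8
- g, slope of the T2 score on true severity, in SD units: 0.5
- D, true severity gap between settings: 0.3 to 0.5 SD
- r, correlation between the errors of QIDS-C and QIDS-SR: 0 or 0.5; both forms are taken as equally reliable
- n = 216 per group, from the document's planned 300 after 10% attrition and 20% mismatch loss (300 × 0.9 × 0.8)

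**Step 1: the outcome form does not matter.** If T0 − T2 = a + b·T0 + c·setting, then T2 = −a + (1 − b)·T0 − c·setting. Modelling change adjusted for T0 gives the same setting coefficient as modelling T2, with the sign reversed.

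**Step 2: bias with QIDS-C alone.** Bias = g(1 − λ)D.
- Largest: 0.5 × 0.4 × 0.5 = 0.10 SD
- Smallest: 0.5 × 0.2 × 0.3 = 0.03 SD
- At D = 0 it is zero.

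**Step 3: bias with both forms.** The error variance of one rating relative to true severity is e = (1 − λ)/λ. For the mean of two it is e(1 + r)/2, so the combined reliability is λ₂ = 1/(1 + e(1 + r)/2) and the bias is g(1 − λ₂)D. For λ = 0.6 and r = 0: e = 0.667, λ₂ = 1/1.333 = 0.75, bias at D = 0.5 is 0.5 × 0.25 × 0.5 = 0.0625.

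| λ | QIDS-C alone, D = 0.3 / 0.5 | Both, r = 0 | Both, r = 0.5 | Removed, r = 0 | Removed, r = 0.5 |
|---|---|---|---|---|---|
| 0.6 | 0.060 / 0.100 | 0.038 / 0.063 | 0.050 / 0.083 | 38% | 17% |
| 0.7 | 0.045 / 0.075 | 0.026 / 0.044 | 0.036 / 0.061 | 41% | 19% |
| 0.8 | 0.030 / 0.050 | 0.017 / 0.028 | 0.024 / 0.039 | 44% | 21% |

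**Step 4: effect on the test.** With SE = √(2(1 − g²λ)/216), the two-sided 5% test of no setting difference rejects in about 6% (λ = 0.8, D = 0.3) to 20% (λ = 0.6, D = 0.5) of studies when the settings are truly equivalent. With QIDS-SR added this is about 5% to 11% for r = 0 and 6% to 16% for r = 0.5.

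**Step 5: the eligibility cut and how patients reach a setting.** A simulation with the QIDS-C > 10 entry rule, g = 0.5, D = 0.4 and λ = 0.7 gave a bias of −0.056 SD, or −0.034 SD with the second form (independent errors). The formula without the cut gives 0.5 × 0.3 × 0.4 = 0.06, so the entry rule adds nothing material. When setting was assigned on the observed QIDS-C score, the bias was about zero.

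**Step 6: predictor analysis, one test only.** With 540 patients (600 × 0.9), λ from 0.7 to 0.9 and g from 0.4 to 0.6, take a scale that correlates 0.3 to 0.5 with true severity and has no effect of its own. It reaches nominal 5% significance in 6% to 76% of studies with QIDS-C alone, 5% to 38% with a second form (r = 0), and 6% to 60% with r = 0.5.

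**The case against.** The strongest reply is that adjusting a QIDS-C outcome for its own baseline is standard practice, and that nothing in the article is contradicted. That is true: this is an improvable choice, not a mistake.

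Three stronger readings are tempting, and the documents do not support them.

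- *The setting contrast is biased.* No severity gap is reported anywhere, and nothing says severity drives the choice of setting. The bias is zero if true severity is balanced, and about zero if setting follows the observed score. Matching on comorbidity, previous episodes and episode duration may also carry some severity information, which the calculation ignores.
- *The predictor list will fill with severity proxies.* The percentages in Step 6 are for one nominal test. The plan is a hierarchical selection for the linear model, and bootstrapping or LASSO for the categorical outcome; neither was simulated. The Background also defines a prognostic variable as one associated with general outcome, so a scale that carries severity information meets that definition. The caution concerns only claims of prediction beyond symptomatology.
- *QIDS-SR is left out of both analyses.* Statistical analysis names no severity instrument, and the grouping of T0 variables into predictor classes does not exclude QIDS-SR. Reliance on one rating is established only for the setting comparison.

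It is also fair to say that the gain is modest. Both forms rest on the same patient's account, so their errors are probably correlated and the smaller reduction is the more plausible one.

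What stands is that the article does state its control set for the setting comparison, and that set omits an available measure of a confounder that is not matched.

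**Conclusion.** The point holds as a conditional one. If true severity differs between settings beyond what one QIDS-C rating captures, residual confounding of about 0.03 to 0.10 SD can remain, which is 15% to 50% of the planning effect d = 0.2. Adding QIDS-SR removes about 40% of it with independent errors (38% to 44%) and about 20% with an error correlation of 0.5 (17% to 21%). It reduces the problem and does not abolish it. These sizes rest on assumed reliability, slope, gap and error correlation; the documents give none of them.

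For the predictor analysis the conclusion is narrower: results presented as going beyond symptomatology should be shown to survive fuller control of severity.

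**What to change.** - **Setting comparison:** in the hierarchical linear model, adjust for T0 QIDS-C and T0 QIDS-SR together, and say so where the control variables are listed. A sensitivity analysis over assumed reliability and error correlation would show how much residual severity could still matter.
- **Predictor analysis:** enter T0 QIDS-SR with T0 QIDS-C in the severity block before testing personality, coping and interpersonal variables, at least as a sensitivity analysis.
- **Leave SCL-90-R out of the forced severity block.** Table 2 lists it under overall disturbance and functioning, and forcing it in could absorb prognostic signal the study wants to find.

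The cost is one extra covariate and a change of wording; the data are already being collected. QIDS-SR can no longer be reported as a separate predictor in a model where it is forced in.

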### Outcomes

The Quick Inventory of Depressive Symptomatology QIDS-C (expert rating) is chosen as the main outcome criterion. The QIDS is a 16-item version of the Inventory of Depressive Symptomatology (IDS), which shows high correlations with other instruments for the measurement of depressive symptomatology [23]. It´s a common, internationally used, licence-free instrument which has a self-report and an expert rating form [23]. The QIDS was chosen as its total score is also used as the main outcome criterion in a large trial on outpatient psychotherapy for chronic depression that is currently conducted in Germany (“LAC-study”, [39]).

We aim to assess outcome dimensionally (change on the QIDS-C score from admission to the three-months follow-up) as well as categorically: a symptom reduction < 20% is defined as “no effect”, a symptom reduction between 20% and 50% as modest change, a symptom reduction of > 50% as partial remission and a symptom reduction of 100% as complete remission (falling below the cut-off value of depression of the QIDS-C) [3,40].

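### The inpatient versus day hospital comparison is to be adjusted for psychotherapy sessions after discharge, a post-treatment variable, so the adjusted estimate may not be the total effect of setting

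*Protocol article*

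**What the plan says.** All references are to the protocol article.

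- *Methods* describes step II as "a comparison of inpatient and day clinic treatment in a quasi-experimental design".
- *Methods against bias* opens with the matching rules: "To compare inpatient and day clinic samples, a parallelization according to known predictors of outcome". The next paragraph sets the covariates. Alongside antidepressant medication and the QIDS-C at admission, it states that "the number of psychotherapy sessions following discharge will be controlled for in the final analysis".
- *Outcomes* defines the dimensional outcome as "change on the QIDS-C score from admission to the three-months follow-up". *Discussion* places the follow-ups 3 and 12 months after discharge.
- *Statistical analysis* adds: "The difference (T0-T2) will be controlled for baseline (T0) severity". It also says "Moderator and mediator analyses will be conducted according to Kraemer et al", without linking that analysis to aftercare.
- The note to Table 2 (*Measurement time points*) puts outpatient treatment after the hospital stay at T2 and T3, and treatment before admission at T0. QIDS-C is also rated at discharge (T1), but discharge severity is not among the listed covariates.

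The article states no direct-effect estimand and mentions no setting comparison without the sessions covariate.

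**The concern.** A covariate protects a non-randomised comparison when it reflects differences that existed before exposure. Sessions after discharge do not qualify, because they follow the exposure. They may also be part of its result: one setting may lead to more aftercare than the other, and patients who leave hospital less well may seek more.

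If either link exists, holding sessions constant takes away part of what the setting did, or partly holds the discharge result constant. It can also bring in unmeasured causes, such as chronicity, that drive both sessions and T2 severity. The coefficient for setting would then be neither the total effect nor a clean direct effect. The stake is the answer to the comparative question, given by a rule that sits in the section meant to limit bias. *Discussion* lists health care use after discharge among the data for an economic analysis, so the article itself treats aftercare as a result in another place.

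**Working it through.** **Timing.** Setting is fixed at admission (T0), and hospital treatment ends at T1. Sessions accrue from T1 onward and are recorded at T2 and T3. The outcome is taken at T2. The order is setting, discharge status, sessions, T2 outcome. A variable in third place cannot confound the first.

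**Size of the shift.** The article gives no figure to reproduce. In a linear model the following identity holds:

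adjusted effect = total effect − (slope of outcome on sessions, given setting and T0 covariates) × (difference in sessions between settings, given T0 covariates).

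The shift is zero if the settings do not differ in sessions, or if sessions are unrelated to outcome within setting. With assumed session differences of 0.2 to 0.5 SD and slopes of 0.1 to 0.3, it runs from 0.2 × 0.1 = 0.02 SD to 0.5 × 0.3 = 0.15 SD. A middle case is 0.3 × 0.2 = 0.06 SD, which is 0.06 / 0.2 = 30% of the planned d = 0.2 (*Sample size calculation*).

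**Illustrative simulation** (2,000,000 records per row; every path size is an assumption):

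- Discharge severity D = −τ·setting + g·U + noise, with variance 1 within setting. U is an unmeasured cause such as chronicity.
- Sessions M = a·setting + b·D + c·U + noise, with noise SD 1.
- T2 severity Y = D + 0.5·g·U + noise, with noise SD 0.5. Sessions themselves have no effect on Y.
- Effects are reductions in Y, in SDs of Y.

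| Scenario | τ | a | b | c | g | Without sessions | With sessions |
|---|---|---|---|---|---|---|---|
| Sessions driven by discharge severity | 0.2 | 0 | 0.3 | 0 | 0.3 | 0.167 | 0.153 |
| Same, stronger | 0.2 | 0 | 0.5 | 0 | 0.5 | 0.158 | 0.122 |
| Same, U also drives sessions | 0.2 | 0 | 0.5 | 0.3 | 0.5 | 0.161 | 0.118 |
| Setting also raises sessions | 0.2 | +0.3 | 0.3 | 0 | 0.3 | 0.171 | 0.231 |
| Setting also lowers sessions | 0.2 | −0.3 | 0.3 | 0 | 0.3 | 0.168 | 0.080 |
| No effect on outcome, setting raises sessions | 0 | +0.3 | 0.3 | 0 | 0.3 | −0.002 | 0.073 |
| Same, stronger, U also drives sessions | 0 | +0.3 | 0.5 | 0.3 | 0.5 | −0.001 | 0.126 |
| No effect on outcome or sessions | 0 | 0 | 0.5 | 0.3 | 0.5 | −0.001 | 0.000 |

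**Hand check of row 4.**

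- Slope of Y on M within setting: 0.3 × (1 + 0.5 × 0.09) / (1 + 0.09) = 0.3135 / 1.09 = 0.288.
- Session difference: 0.3 − 0.3 × 0.2 = 0.24.
- SD of Y: √(1 + 0.09 + 0.25 × 0.09 + 0.25 + 0.2²/4) = √1.3725 = 1.172.
- Total effect: 0.2 / 1.172 = 0.171.
- Adjusted effect: (0.2 + 0.288 × 0.24) / 1.172 = 0.230.

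This agrees with the simulated row. Adjustment can shrink, inflate or create a setting effect, or leave it unchanged.

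**The case against.** The strongest defence is that aftercare is a co-intervention before T2, so the effect of the hospital phase net of aftercare is a legitimate question. That is true, but the article does not state this estimand. Plain adjustment would deliver it only if the common causes of sessions and outcome were controlled, and discharge severity is not listed.

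Settings are not randomised, so sessions could also stand in for access to outpatient care that differed before admission. Dropping them would therefore not guarantee less total bias. This stands as a limit. Previous treatment for depression, recorded at T0, covers some of that ground without the timing problem.

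The size is uncertain. When sessions depend only on discharge severity (first two rows), the shift is 0.014 to 0.036 SD. With 200 per group the standard error of d is about √(2/200) = 0.10, so that is under half a standard error. Larger shifts need an assumed setting difference in aftercare. The illustrations also address only the main effect of setting, whereas the hypothesis under *Objectives and hypotheses* concerns depression type and differential outcome.

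Two stronger readings are tempting and not supported:

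- A reader might infer that the adjustment certainly biases the result. The documents do not show that setting or discharge status changes the number of sessions.
- A reader might infer that the antidepressant covariate has the same fault, since Table 2 says "Additionally assessed at all time points of measurement: pharmacological treatment, somatic diagnoses". *Methods against bias* does not say which value enters the model, and an article may leave that to the full protocol or analysis plan. It is not a finding.

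**Conclusion.** The point holds in limited form. The article explicitly names a post-treatment variable as a control in the setting comparison. The variable is not a confounder of setting, and the adjusted coefficient would differ from the total setting effect whenever sessions differ between settings and are related to outcome within setting. That conclusion rests on the timing in the document alone. The figures rest on assumed path sizes: they show that the shift could be trivial, or could be comparable with the planned d = 0.2, in either direction. They do not estimate what will happen in this study. The fault can be corrected before analysis and does not touch the design or the data collection.

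**What to change.** 1. Make the main inpatient versus day hospital comparison adjust only for variables fixed at T0: initial QIDS-C and other baseline predictors, including previous treatment for depression.
2. Report the number of sessions after discharge by setting, descriptively.
3. Use sessions in a model only in a separately labelled mediation or sensitivity analysis that states its direct-effect estimand. There, T1 QIDS-C is a confounder of sessions and outcome that is itself affected by setting. Entering it as an ordinary covariate would block the part of the setting effect that runs through discharge status. A method built for such confounders is needed, for example a marginal structural model with inverse probability weights, or sequential g-estimation.

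The cost is a short change to the analysis text, since all the variables are already collected. There is a small downside: the main estimate will include any effect of setting that runs through aftercare, so the net-of-aftercare question moves to the secondary analysis.
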